## Abstract

**Background:**

Patients on maintenance hemodialysis (MHD) frequently complain of insomnia. Poor sleep quality impairs their quality of life and adversely affects long-term outcome. Previously we applied auricular acupressure therapy (AAT) for MHD patients with insomnia and yielded favorable results. AAT probably improves sleep quality by stimulating the vagus nerve and inhibiting sympathetic overactivity. However, the efficacy of AAT for insomnia in this population is still lacking. The proposed randomized controlled trial (RCT) will evaluate the efficacy and safety of AAT for improvement of sleep quality in MHD patients with insomnia.

**Methods/design:**

The proposed study is a multi-center, double-blind (participants and assessors), parallel-group RCT. A total of 112 participants with insomnia will be recruited from six hemodialysis centers in Guangzhou, China, and randomly allocated in a 1:1 ratio to receive auricular acupressure on either active points (AA group) or control points (points irrelevant to insomnia management, SAA group). The treatment will last for 8 weeks prior to a follow-up period of 12 weeks. Evaluation by blinded assessors at baseline, at 8 weeks (end of treatment) as well as at 4-week, 8-week and 12-week follow-ups (after intervention) will include Pittsburgh Sleep Quality Index (PSQI) scores and average weekly dose of hypnotics. The primary endpoint is clinical response rate (percentage of participants who reach a reduction of PSQI global score ≥ 3 in each group) at 8 weeks from baseline. Secondary endpoints include the changes in PSQI scores over time from baseline, as well as the changes in weekly dose of hypnotics.

**Discussion:**

This paper describes the rationale and design of a double-blind RCT that aims to determine the efficacy and safety of AAT for insomnia of hemodialysis patients. If successful, this project will provide evidence of the efficacy and safety of AAT for insomnia of hemodialysis patients.

**Trial registration:**

ClinicalTrials.gov, Identifier: NCT03015766. Registered on 22 December 2016.

**Electronic supplementary material:**

The online version of this article (10.1186/s13063-018-2546-2) contains supplementary material, which is available to authorized users.

## Background

Sleep disorders, such as insomnia, restless leg syndrome, sleep apnea and excessive daytime sleepiness, are common in patients with end-stage renal disease (ESRD), especially in those receiving dialysis [1]. Insomnia is one of the most common conditions, with a prevalence rate as high as 49–84.5% depending on the specific population [2–5]. Poor sleep quality is known to have adverse effects on patients’ health-related quality of life [6], mental health [7], social adaptability [8] and even long-term survival [9].

ESRD patients with insomnia share common risk factors identified in the general population, such as female sex, advanced age, lack of physical activity and depressed mood [10]. In addition, multiple factors, including chronic kidney disease (CKD) and renal replacement therapy, also play roles in the development of insomnia. CKD comorbidity (e.g., diabetes) and CKD-related complications (e.g., uremia, anemia and hyperparathyroidism) are all recognized factors [5, 11, 12]. Somatic symptoms, such as pruritus, bone pain and arthralgia, are also related to impaired sleep quality in dialysis patients [13].

Poor sleep quality prompts physicians to prescribe hypnotics (usually benzodiazepines) for hemodialysis (HD) patients, which may be associated with adverse effects, such as memory impairment, drug resistance, dependence and addiction [14]. Current guideline for chronic insomnia suggests that sleep medications should be properly used based on awareness of both effectiveness and harms [15]. Despite concerns regarding safety and dependency of long-term usage of hypnotic drugs expressed by both physicians and patients, a considerable proportion (benzodiazepines: 42.6% and hypnotics: 20.0%, in single-center cross-sectional study [16]) of HD patients continue to take nightly sleep medications for prolonged periods while at the same time complaining of unsatisfactory sleep quality. Therefore, both caregivers and patients are confronted with the conflicting requirements of improving patients’ sleep quality and reducing their dependence on hypnotics.

Non-pharmacological therapies with supportive evidence of a hypnotic effect are desirable. Auricular acupressure therapy (AAT), a therapeutic approach that treats various disorders by stimulating specific points on the ear, is a popular form of complementary medicine in China. Kung’s study in Taiwan among women with postmenopausal insomnia indicated that AAT led to increased cardiac parasympathetic activity and reduced cardiac sympathetic activity with improvement of sleep quality [17]. In another investigation in women with postpartum insomnia [18], patients receiving AAT for 2 weeks showed decreases in Pittsburgh Sleep Quality Index (PSQI) total scores from 8.7 (pre test) to 5.57 (post test, 36% reduction). Scores on the subscales of PSQI also showed significant improvement of sleep quality. Autonomic nervous system regulation by the auriculovagal afferent pathway [19] has been proposed to explain how AAT improves sleep quality. The auricular branch of the vagus nerve links the acupressure stimulation and vagal regulation. AAT might trigger vagal regulation and correct the overactivity of sympathetic nerves which plays a crucial role in chronic hemodialysis patients with insomnia [20]. Therefore, auricular acupressure might be effective in improving sleep quality for hemodialysis patients.

Our previous study showed improvements in sleep quality and reduced consumption of sleep medications (6.98 ± 4.44 pills per week post AAT compared with 4.23 ± 2.66 pills per week pre AAT, *P* < 0.01) after a 4-week course of AAT in addition to basic care in hemodialysis patients with severe insomnia [21]. In a pilot randomized controlled trial (RCT), we found that AAT on specific points with an appropriate rationale yielded a higher response rate in PSQI score improvement than that on sham points (62.5% vs. 32.3%, *χ*^2^ = 5.77, *P* = 0.02) [22]. However, these previous studies had some limitations. Data collected from a single center may lack the scientific rigor or external validity required to support widespread application of AAT. In addition, sample size was not calculated to guarantee sufficient statistical power. Owing to design limitations, the efficacy and safety of AAT in hemodialysis populations with insomnia have yet to be confirmed. Therefore, we aim to perform a full-scale RCT to test the hypothesis that AAT is an effective and safe means of improving sleep quality and reducing dependence on hypnotics in hemodialysis patients.

## Methods/design

### Study design

The study uses a two-arm, randomized, double-blind, sham-controlled design. The trial will be performed in six hemodialysis centers in Guangdong Province, People’s Republic of China, all of which are tertiary hospitals of Chinese Medicine: Guangdong Provincial Hospital of Chinese Medicine, Guangzhou Charity Hospital, Guangzhou HEMC (Higher Education Mega Center) Hospital, Guangzhou Hospital of Traditional Chinese Medicine, Wuyi Hospital of Traditional Chinese Medicine and Shenzhen Hospital of Traditional Chinese Medicine. This trial will include an 8-week treatment period and a 3-month follow-up period (visits at 4-week intervals). Eligible subjects will be randomized into one of the two arms in a ratio of 1:1 to receive AAT on either active points or sham points. The trial has been registered at ClinicalTrials.gov (NCT03015766).

### Participants

We will include patients receiving regular hemodialysis treatment for more than 3 months and less than 10 years. These patients are more likely to go through the whole trial which will continue for 5 months. Incident hemodialysis patients (less than 3 months) and those who have been on dialysis for more than 10 years usually have a high mortality rate [23, 24]. Patients will have initial assessment of sleep quality and physical examination to meet the diagnosis of chronic insomnia. Potentially eligible participants are being identified through screening of patient medical records at each dialysis center. Screening of patients in each center will be performed by one assigned personnel according to the inclusion and exclusion criteria. A flow chart of the participant recruitment is shown in Fig. 1.

**Fig. 1 Fig1:**
[figure not shown]
Trial flow chart

### Participant timeline

The time course for participant recruitment, intervention, assessment and follow-up is shown in the Standard Protocol Items: Recommendations for Interventional Trials (SPIRIT) Figure (Fig. 2).

**Fig. 2 Fig2:**
[figure not shown]
Standard Protocol Items: Recommendations for Interventional Trials (SPIRIT) Figure. Timing of visits and data collection. Abbreviations: AA auricular acupressure, SAA sham auricular acupressure, PSQI Pittsburgh Sleep Quality Index

### Inclusion criteria

Subjects fulfilling all of the following criteria will be included:Aged 18–75 years (either sex).On regular hemodialysis (two or three sessions every week, 4 h each session, total weekly dialysis period ≥ 10 h)Insomnia diagnosed according to *The Diagnostic and Statistical Manual of Mental Disorders, Fifth Edition* (DSM-5) [25]Baseline global PSQI score > 7Informed consent provided

### Exclusion criteria

Patients with any of the following conditions will be excluded:Presence of comorbidities including cancer, congestive heart failure, connective tissue disease and hematological diseasesInadequately dialyzed, indicated by urea clearance index (KT/V) < 1.20Presence of severe physical symptoms, such as bone pain, itchy skin, sleep apnea and restless legs, which are obviously causative of insomnia; and exhaustion caused by severe anemia (hemoglobin < 60 g/L) or malnutrition (serum albumin < 30 g/L)

### Randomization and allocation concealment

Subjects will be randomly allocated into one of the two treatment arms in a 1:1 ratio: (1) treatment group (AA group) and (2) control group (SAA group). Central randomized allocation will be performed. Patients will be stratified based on six sites and randomly assigned to one of the two groups. The Chinese Clinical Trial Registry will generate the random number sequence using computer software, and will deposit the allocation sequence in ResMan^®^ Clinical Trial Management Public Platform, a web-based database. When a new participant is enrolled in the study, the research coordinator of each site will apply for the allocation information through this online system and assign participants to interventions accordingly. It is not possible to speculate on the allocation status of the participant before obtaining this information. The other personnel, including research nurses, assessors and clinical physicians, are not authorized to apply for random numbers. All processes will be recorded and saved appropriately.

### Blinding

Both the participants and the assessors in this trial will be blinded to the allocation. AAT will be provided by trained nurses and manipulated by patients. The nurses and patients will be told that we are comparing two different treatment protocols (TPs), in which all auricular points involved are named as numbers with specific defined locations. We will have two nurses in each site assigned to perform the intervention. One will be responsible for providing TP A and the other for TP B. The assignment of nurses is done by drawing lots. The nurses will receive researcher training before the trial. They are required to perform auricular acupressure following the standard procedure, no matter what TP they are practicing. They are also required not to discuss the difference between the two TPs with patients. To avoid differences due to the Hawthorne and Rosenthal effect [26, 27], we will script the nurses to limit their interaction with the participants. Any additional questions will be directed to the research coordinator of each center. All results will be reported to another investigator responsible for assessing sleep quality in a clinical interview. The investigator will provide questionnaires to participants at the scheduled time for assessment. Clinical physicians of the Hemodialysis Department are allowed to prescribe estazolam (14 tablets each time) when patients require. At the end of the week, the patients should return the tablets left and obtain a new prescription if they need. All personnel will be properly assigned before the start of the trial.

### Interventions

AAT is based on the theory that specific points on the auricle correspond to major organs or systems of the body and that the function of the targeted organ or system can be modulated by manipulating corresponding auricular acupoints. AAT applies stimulation through pressure on specific acupoints using embedded beads, usually *Semen vaccariae* seeds (*Wang Bu Liu Xing*) or stainless steel beads. This approach is non-invasive, and recipients can be trained to manipulate the beads themselves to exert stimulation at a required frequency. A map of commonly used auricular acupoints is shown in Fig. 3a.

**Fig. 3 Fig3:**
[figure not shown]
A demonstration of interventions in the trial. **a** A map of auricular acupoints commonly used. **b** Ear-press seed (Wang Bu Liu Xing) applied in this trial. **c** Acupoints of both groups in the trial

In this trial, two research nurses for each center will be assigned to administer AAT to participants. They will gain approval from licensed acupuncturists through training and competence assessment before the start of the trial. They will provide AAT for patients during dialysis sessions for eight consecutive weeks. A standard procedure of AAT has been established as follows:Identify the ear points according to the TP directed by the research coordinator.Sterilize the involved area of the ear with 75% isopropyl alcoholAttach an adhesive plaster (size: 1.0 cm × 1.0 cm) with one bead (*Semen vaccariae*, globes approximately 2.0 mm in diameter; surface: smooth; colour: black; Taicheng Technology & Development Co., Ltd., Shanghai, China) embedded in each acupoint (Fig. 3b)Provide instructions to press the beads with appropriate strength (approximately 0.3–0.4 kg) and rate (one to two beats per second) for 1 min at each point [28]. This should be done three times during the day and once in the eveningThe plasters will be replaced with fresh ones every 2–3 days (usually on the dialysis day) depending on the dialysis schedule. If the plasters or beads become detached, participants should come to the hospital to receive fresh plasters. To improve their adherence to interventions, we plan to attach the auricular acupressure beads when the patients come for their scheduled dialysis and replace the beads every 2–3 days (on the dialysis day as well). Activities during each visit in the treatment period will be documented in the Case Report Form.

### Treatment group

Participants in the treatment group (AA group) will receive AAT on five active acupoints:Acup.1. *Shen Men* (Spiritual Gate, TF4)Acup.2. *Jiao Gan* (Sympathetic autonomic, AH6a)Acup.3. *Xin* (Heart, CO15)Acup.4. *Pi Zhi Xia* (Subcortex, AT4)Acup.5. *Nei Fen Mi* (Endocrine, CO18)

The rationale for selecting these points has been explicitly described previously [21, 22]. Briefly, these points were selected based on Traditional Chinese Medicine (TCM) meridian theory, results of an academic literature review, and on-site clinical practice experience [29]. These points help patients sleep by regulating the autonomic nervous system. These points are anatomically connected to the auricular branch of the vagus nerve. Stimulation on these points may increase parasympathetic activities and reduce sympathetic activities [30, 31], which play an important role in sleep [32].

### Control group

Participants in the control group (SAA group) will receive AAT on five helix points (HX 5–9), which are clearly remote from the inner ear area. These points lack evidence for insomnia management. In our pilot study, these points had minor effects on sleep quality, which could not be differentiated from the placebo effect.

The acupoints in both groups are illustrated in Fig. 3c. The locations of these points in both groups are listed in Table 1, following the National Standards of the Nomenclature and Location of Auricular Acupoints published in China [33].

**Table 1 Tab1:** Locations of auricular acupoints used in the trial

Auricular acupoints	Locations
AA group	
TF4	At the apex of the triangular fossa, in the bifurcating point between superior and inferior crura of the antihelix
AH6a	At the end of the inferior antihelix crus
CO15	Around the central depression of the cavum conchae
AT4	At the medial side of the antitragus
CO18	In the intertragic notch, at the medial inferior part of the cavum conchae
SAA group	
HX 5	An area on the helix, between the two feet of the antihelix
HX 6	An area on the helix, between the upper foot of the antihelix and the apex conchae auris
HX 7	An area on the helix, between the apex conchae auris and the helix tubercle
HX 8	An area on the helix, and at the helix tubercle
HX 9	An area on the helix, and below the helix tubercle

*AA* auricular acupressure, *AAT* auricular acupressure therapy

### Sample size estimation

In a pilot RCT conducted previously, the clinical response rates of AAT and sham AAT were 62.5% and 32.3%, respectively [22]. With these data, we used the following formula to calculate the estimated sample size [34].$$ \mathrm{N}\kern0.5em =\kern0.5em \frac{{\left({u}_{\alpha }+{u}_{\beta}\right)}^2\left(1+\raisebox{1ex}{$1$}\!\left/ \!\raisebox{-1ex}{$\mathrm{k}$}\right.\right)p\left(1-p\right)}{{\left({p}_e-{p}_c\right)}^2},\kern0.5em p\kern0.5em =\kern0.5em \frac{p_e+{kp}_c}{1+k} $$

In this formula, *k* (the ratio of allocation) = 1, *u*_a_ and *u*_*β*_ are 1.6449 and 1.2816, respectively, when 90% statistical power (*β* = 0.1) is required and a significance level of 5% (*α* = 0.05) is allowed. Here, *p*_e_ represents the incidence rate of the treatment group, while *p*_c_ represents that of the control group. Therefore, we will require at least 56 subjects in each group taking into account an allowed dropout rate of 15%. The results have been confirmed using PASS software 11.0 (NCSS, LLC, Kaysville, UT, USA) by tests for two independent proportions.

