### Statistical analysis

Statistical analysis will be performed using SPSS Statistics Software 22.0 (IBM Corp., Armonk, NY, USA). For the results of the study, means ± standard deviations will be calculated for normally distributed quantitative variables and median (interquartile range) for non-normally distributed variables. In addition, the 95% confidence interval around the mean will be presented. For categorical variables, the number and percentage of patients within each category will be presented.

Statistical analyses of primary and secondary outcomes will be conducted as follows. First, all analyses will be based on the intention-to-treat (ITT) principle. All patients enrolled in the study will be included in the analyses, regardless of whether they complete the treatment or adhere to the protocol. Data distribution is expected to be normal, and skewed distribution data will be transformed prior to analysis. Then, the outcome of the clinical response will be analyzed by the c*hi*-squared test or Fisher’s exact test. For the secondary outcomes, repeated-measures analyses of variance (rANOVA) will be conducted to compare the changes in PSQI scores and the weekly dose of hypnotics at 8, 12, 16 and 20 weeks from baseline. Missing values will be addressed using the method of last observation carried forward (LOCF). To avoid potential confounding factors, additional sensitivity analyses will be performed following these statistical analyses.

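### The sample size uses a one-sided 5% critical value, but the primary test is non-directional, so the stated 90% power is not delivered

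*Protocol article*

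**What the plan says.** The Sample size estimation section plans on pilot results in which "the clinical response rates of AAT and sham AAT were 62.5% and 32.3%, respectively". It sets "the ratio of allocation) = 1" and "a significance level of 5" percent, and says that the two quantiles "are 1.6449 and 1.2816, respectively, when 90% statistical power" is wanted. From these it concludes that "we will require at least 56 subjects in each group taking into account an allowed dropout rate of 15" percent. It adds that PASS 11.0 confirmed the result "by tests for two independent proportions", without giving the number of sides used there.

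The Primary outcome measurement section defines the endpoint as a between-group difference in response rates at 8 weeks and gives no direction. In the Statistical analysis section "the outcome of the clinical response will be analyzed by the" chi-squared test or Fisher's exact test, again with no one-sided alternative. Nowhere does the article declare a one-sided hypothesis, significance level or decision rule.

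**The concern.** The power calculation and the primary analysis appear to belong to different tests. Pearson's chi-squared test on a 2×2 table is non-directional, and Fisher's exact test is two-sided unless a one-sided version is declared. Reading α = 0.05 as two-sided also fits the pilot result in the Background section: χ² = 5.77 with P = 0.02 is the ordinary two-sided P value.

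Two things are at stake. First, a null result would be read as coming from a trial with 90% power when the power is lower. This matters here because the Background section criticises the earlier studies for not calculating a sample size that guaranteed power, and the Discussion lists the sample size among the safeguards against bias. Second, undeclared sidedness leaves room to choose after the data are seen. With the effect in the favourable direction, a two-sided P between 0.05 and 0.10 could be called a success by pointing to 1.6449.

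**Working it through.** **Inputs.** From Sample size estimation: p_e = 0.625, p_c = 0.323, k = 1, u_α = 1.6449, u_β = 1.2816, dropout 15%. Derived: p = (0.625 + 0.323)/2 = 0.474; 1 − p = 0.526; difference = 0.302.

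**1. Reproducing the stated 56.** The protocol's formula with k = 1 is N = (u_α + u_β)² × 2p(1 − p)/(p_e − p_c)².

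- (1.6449 + 1.2816)² × 2 × 0.474 × 0.526 / 0.302² = 46.8, rounded up to 47.
- 47/0.85 = 55.3, rounded up to 56 per group, 112 in total. This matches exactly.

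**2. The same formula for a two-sided 5% test.**

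- (1.96 + 1.2816)² × 2 × 0.474 × 0.526 / 0.302² = 57.5, rounded up to 58.
- 58/0.85 = 68.2, rounded up to 69 per group, 138 in total.

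At 90% power, then, the protocol's formula gives 56 only with the one-sided quantile.

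**3. A second formula as a check.** The Fleiss formula uses the pooled variance under the null hypothesis and the separate variances under the alternative: n = [u_α√(2p(1 − p)) + u_β√(p_e(1 − p_e) + p_c(1 − p_c))]²/(p_e − p_c)². The square roots are 0.7062 and 0.6731.

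- One-sided: [(1.6449 × 0.7062 + 1.2816 × 0.6731)/0.302]² = 44.9, so 45; 53 after dropout.
- Two-sided: [(1.96 × 0.7062 + 1.2816 × 0.6731)/0.302]² = 55.3, so 56 before dropout; 66 after.

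On this formula 56 per arm reaches two-sided 90% only if nobody drops out.

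**4. Two-sided 5% power of the planned size.**

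By the protocol's own formula at 47 per arm: the standard error is √(2 × 0.474 × 0.526/47) = 0.1030, 0.302/0.1030 = 2.932, 2.932 − 1.96 = 0.972, and Φ(0.972) = 0.834.

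By the Fleiss formula at 47 per arm: (0.302 × √47 − 1.96 × 0.7062)/0.6731 = 1.020, and Φ(1.020) = 0.846.

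Exact power, by summing binomial probabilities over all 2×2 tables:

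| Case | Per arm | Rates | Chi-squared (uncorrected) | Fisher |
|---|---|---|---|---|
| 15% dropouts leave the analysis | 47 | 62.5% vs 32.3% | 84.6% | 79.0% |
| No dropout | 56 | 62.5% vs 32.3% | 89.8% | 85.9% |
| 15% lost before week 8, counted as non-responders | 56 | 53.1% vs 27.5% | 79.4% | 73.7% |

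The third row assumes equal 15% loss in both arms, all before week 8; the article does not give the timing. Its rates are 0.85 × 62.5% = 53.1% and 0.85 × 32.3% = 27.5%.

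**5. The authors' own convention.** The pilot rates fit 20/32 and 10/31 (counts inferred from the percentages). These give χ² = 5.77 and a two-sided P of 0.016, which rounds to the printed 0.02.

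**The case against.** The strongest reply is that 47 is the wrong number. The Statistical analysis section includes everyone enrolled and fills gaps by LOCF, and the Primary outcome measurement section divides by all participants in the group. The analysed number is then 56 per arm, where chi-squared power is about 90%. The change of denominator is real, but it does not restore the power. The Outcome measurement section schedules no PSQI between baseline and week 8, so a participant lost before week 8 has only the baseline score to carry forward and counts as a non-responder. If all of the 15% are lost that way, power is 79.4%, below the 47-per-arm figure. The power nears 90% only if dropouts do not dilute the rates, for instance because the pilot rates already include them, which the article does not say.

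Other replies carry some weight:

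- Fisher's test is usually a fallback for sparse tables. With 47 per arm the smallest expected count is about 0.474 × 47 = 22, so chi-squared is the likelier test and its 15–17% false-negative risk the likelier figure. The article still leaves the choice open.
- Sidedness is inferred, since the analysis section is silent, and the aim in the Background is worded directionally. A directional aim is not a declared one-sided test.
- The PASS check settles nothing, because its sidedness is not given.
- The arithmetic is right for a one-sided test, and a two-sided 5% test would still control the type I error. What is overstated is the power.
- Uncertainty in the pilot rates is larger than this shortfall: the inferred counts give a 95% interval for the difference of about 7 to 54 percentage points. That is a separate weakness and does not make the 90% claim correct.

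**Conclusion.** The concern holds. The calculation is for a one-sided 5% test, while the planned primary test is non-directional and no one-sided rule is declared. At the planning rates and with the protocol's own 15% dropout (47 evaluable per arm), two-sided 5% power is 83–85% by chi-squared and about 79% by Fisher's test. That is 5 to 11 percentage points below the stated 90%.

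These figures take the pilot rates as true and remove dropouts from the analysis. Keeping early dropouts as non-responders lowers chi-squared power to about 79%; no dropout at all raises it to about 90%. The shortfall is moderate and the trial is not grossly underpowered, but the stated power belongs to a test other than the one planned and has to be corrected.

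**What to change.** - In Sample size estimation and Statistical analysis, state that the primary test is two-sided at 5%.
- Replace the 90% claim with what 112 participants deliver: about 84% by chi-squared with 47 evaluable per arm. Give the condition with the figure, and add the ITT/LOCF range of about 79% (all dropouts before week 8 counted as non-responders) to 90% (no dropout).
- Name one primary test: the uncorrected chi-squared test, or its version stratified by site to match the randomisation, in place of the open choice with Fisher's test. The power above was computed for the unstratified test.
- If a one-sided 5% test was truly intended, declare it now with its decision rule, before any unblinded look.

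The cost is wording in two sections and a less favourable power statement. No extra enrolment is needed for the correction. Since recruitment is ongoing, the sponsor could instead restore two-sided 90% power, which takes 138 participants by the protocol's own formula.
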